## Abstract

Supplemental Digital Content is available in the text

## Introduction

1

Lower back pain (LBP) is the leading cause of lost productivity in working age adults due to social and economic hardships of medical rehabilitation.^[1]^ Over 80% of adults report LBP, of which nearly 60% develop severe symptoms that last longer due to poor treatment.^[2]^ Most LBPs are non-specific with no identifiable causes, and conventional treatment often targets only pain relief, leading to poor satisfaction.^[3]^

Korean patients suffering from chronic non-specific lower back pain (cnLBP) prefer traditional Korean medicine (TKM), which utilize multiple personalized and holistic treatment methods. The results of the Korean Medical Use and Consumption Survey conducted in 2017 found cnLBP to be the major reason for visits to Korean medical institutions, with a lifetime healthcare services utilization of 52.7%.^[4]^

*Sogyeonghwalhyeol-tang* (SGHH) finds a mention in the *Wanbinghuichun*, a classical treatise on traditional Chinese medicine, where it is indicated for treatment of abnormal musculoskeletal symptoms such as pain, palsy, and stiffness.^[5]^ It is thought that SGHH functions by rejuvenating blood and dredging the meridians and collaterals.^[6]^ The use of SGHH has been reported in several cases of arthritis-induced pain and neurologic symptoms.^[7–9]^

Chuna manual therapy (CMT) is a therapeutic intervention that stabilizes and maintains orthopedic functions by stimulating the meridian system and correcting displacement of the osteoarticular structure.^[10]^ Randomized controlled trials (RCTs) investigating CMT have demonstrated its efficacy in providing relief from musculoskeletal diseases including cnLBP.^[11]^ Though TKM-based monotherapy is common in RCTs for cnLBP, as it avoids complications arising from interaction effects, the holistic nature of TKM demands multiple interventions. Thus, the integration of multiple modalities such as Chinese *Tuina*, Japanese *Shiatsu*, and American chiropractic and osteopathic medicine, may be considered for cnLBP.

Here, we investigate the efficacy of a combination intervention comprising SGHH and CMT for the treatment of cnLBP. While initially, the trial was based on a 2 × 2 factorial design, an arm consisting of a sham CMT with placebo was considered unethical, due to which the trial will be based on an incomplete factorial design (Table 2).^[12]^

The primary outcome of this study is to determine the efficacy of a combined multidisciplinary approach using SGHH with CMT on cnLBP, compared to SGHH alone. The secondary outcome is to compare the efficacy of SGHH and a placebo on cnLBP.

## Methods

2

### Study setting

2.1

This study will be a multicenter, assessor- and analyst-blinded, incomplete factorial, randomized, parallel group, placebo-controlled clinical trial. Four university-affiliated TKM hospitals and one private secondary care hospital are chosen to be the study sites – Gil Oriental Medical Hospital of Gachon University, Semyung University Second Affiliated Oriental Medical Hospital at Jecheon, Dunsan Korean Medicine Hospital of Daejeon University Woosuk University of Korean Medicine and the Jaseng Hospital of Korean Medicine. Recruitment will be facilitated using hospital on/offline bulletin boards, and local community-based newspaper advertisements.

### Participants

2.2

#### Eligibility criteria

2.2.1

The following conditions will be considered prior to enrollment (Table 1).

**Table 1 T1:**
[figure not shown]
Eligibility criteria.

**Table 2 T2:**
[figure not shown]
Design of the study groups.

#### Randomization

2.2.2

The flow chart describing the trial protocol is shown in Fig. 1. The study population will enroll 150 eligible participants who will undergo a 7-day run-in period prior to randomization. The participants will be randomly allocated to the SGHH group, SGHH with Chuna group or placebo with Chuna group at a ratio of 1:1:1. Random allocation will be facilitated by a web-based application designed by the contract research organization (CRO), the Institute of Safety and Effectiveness Evaluation for Korean Medicine (ISEE), Kyung Hee University. Independent staff from ISEE will use the SAS 6.1 program for randomization list generation and stratification of the trial sites using block sizes of 3 or 6. Once the participant is randomly assigned to a group, patients will not be informed of the type of allocation that they will receive. However, due to diverse intervention strategies, this trial is designed as an assessor- and analyst-blinded study. Participants will be cautioned on confidentiality of allocation prior to outcome assessment and an independent assessor will evaluate allocation in a secured area without seeking information on treatment allocation that the participant will receive. The final dataset will be sent to data analysts without information on treatment allocations to avoid bias in the analysis of study results. In case of expected abnormal symptoms or occurrence of urgent medical conditions, the site's PI will directly inform ISEE and the sponsor to unblind the treatment allocation according to the standard operating procedures (SOPs).

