#### Chuna manual therapy (CMT)

2.3.3

The CMT strategies in this trial are selected after consultation with the scientific committee of the Korean Society of Chuna Manual Medicine for Spine and Nerves (KSCMM).^[14–16]^ Each treatment session conducted by qualified physicians will be 20 to 30 minutes long and will include 3 mandatory and 1 or 2 selective techniques per participant. The CMT physician must be a registered physiatrist of Korean medicine (specialist of physical medicine and rehabilitation) with more than 1 year of clinical experience and should have completed the 126-hour Chuna Manipulative Treatment (CMT) Workshop and have a thorough understanding of study design through an SOP training workshop prior to study initiation. The final selected techniques are presented in detail (Supplemental Digital Content (Appendix 1)).

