#### Primary outcome measurement

2.5.1

We will use numeric rating scale (NRS)^[17]^ as the primary outcome for assessing the severity of LBP, by evaluating intensity of low back pain (LBP) on a scale range of 0 (no pain at all) to 10 (worst pain imaginable). The participants will be asked to rate their pain on a defined scale at each assessment. The changes in the pain intensity between the 3 groups will be analyzed.

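### Site-level blocks of 3 or 6, with sizes printed and CMT visible to treating staff, leave part of the CMT/no-CMT sequence inferable and expose the primary contrast to a risk of selection bias

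*Protocol article*

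**What the plan says.** Section 2.2.2 of the protocol article has patients "randomly allocated to the SGHH group, SGHH with Chuna group or placebo with Chuna group at a ratio of 1:1:1". Independent CRO staff make the list, with "randomization list generation and stratification of the trial sites using block sizes of 3 or 6", and a web application releases the allocations. The section also states that "The study population will enroll 150 eligible participants who will undergo a 7-day run-in period prior to randomization".

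On blinding, the same section says that "due to diverse intervention strategies, this trial is designed as an assessor- and analyst-blinded study". Staff who treat patients are not listed as blinded. Section 2.3.3 describes CMT: "Each treatment session conducted by qualified physicians will be 20 to 30 minutes long". The placebo (2.3.2) is made to resemble SGHH.

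The Introduction gives the primary objective as the efficacy of a "combined multidisciplinary approach using SGHH with CMT on cnLBP, compared to SGHH alone". The primary outcome (2.5.1) is self-rated: "The participants will be asked to rate their pain on a defined scale at each assessment".

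**The concern.** Central allocation hides the list, but it cannot hide assignments already made when one component of treatment is delivered openly at the site. Each past patient is visibly CMT or no CMT, and every block contains these in a fixed 2:1 ratio. With small blocks of known size, the tally so far carries information about the next assignment.

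The visible split is the one that matters most, because it separates the two arms of the primary comparison. If someone involved in enrolment could anticipate the next assignment and acted on it, for instance in whom to put forward or in what order, the SGHH-alone arm could differ in prognosis from the CMT arms. Blinding the assessor and analyst would not correct a difference that existed before treatment. The trial is meant to supply an effect size for larger studies (2.5.4), so a distorted contrast could carry forward.

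**Working it through.** The article gives no predictability figure, so there is none to reproduce.

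**Inputs**
- Block sizes 3 or 6, by site; ratio 1:1:1 (2.2.2). A block of 3 holds 1 no-CMT and 2 CMT places; a block of 6 holds 2 and 4.
- 150 patients (2.2.2). For sites, the Study setting section says: "Four university-affiliated TKM hospitals and one private secondary care hospital are chosen to be the study sites". That is 5 sites, so 150/5 = 30 per site. Equal recruitment is an assumption.
- Sizes equally likely and mixed at random within a site: an assumption, as the article does not say.
- The observer sees the whole past CMT/no-CMT sequence at the site: an assumption, the least favourable case.

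**Block sizes and boundaries known (exact)**
An assignment is certain once only one type remains in the block. With N no-CMT and C CMT places, the expected number of certain assignments per block is C/(N+1) + N/(C+1).
- Block of 3: 2/2 + 1/3 = 4/3, and (4/3)/3 = 44.4%.
- Block of 6: 4/3 + 2/5 = 26/15, and (26/15)/6 = 28.9%.
- Equal mix of 3 and 6: (4/3 + 26/15)/9 = 34.1% in the long run. Simulating sites of 30, where the last block may be cut short, gives 33%.
- Mix of 6, 9 and 12, simulated the same way: 19%.

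**Only the set of sizes known (simulated)**
Here the observer must infer which block is running. From the start of a site, one no-CMT patient settles nothing, because a second may follow in a block of 6. Two no-CMT patients in a row at the start do settle it: the block must be a 6 and the next four are CMT. A Bayesian observer updating in this way over sites of 30 gives:

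| Block sizes | Certain beforehand | Guessed correctly | Gap in predicted P(no CMT) |
|---|---|---|---|
| No information (always guess CMT) | 0% | 66.7% | 0 |
| 3 and 6 | 9.6% | 75.5% | 0.522 − 0.242 = 0.28 |
| 6, 9 and 12 | 2.2% | 71.4% | 0.434 − 0.280 = 0.15 |

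The gap is the mean predicted probability of no CMT among patients who truly got no CMT, minus that among patients who got CMT. Moving to 6, 9 and 12 cuts certain assignments by about four-fifths (9.6% to 2.2%) and roughly halves the gap.

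**Cost in balance**
At 30 patients per site, the mean difference between the largest and smallest arm is about 0.4 patients with 3/6 and 0.9 with 6/9/12. The 95th percentile is 2 for both.

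**The case against.** The strongest reply is that predictability is only partial and the article already has safeguards. Using two block sizes is itself a guard against prediction, the list is made independently and released centrally, and the run-in means that anyone timing enrolment must guess about a week ahead while other patients may be randomised in between. All of this stands and lowers the risk. None of it removes the information in past visible assignments: even with the sizes mixed, guessing beats the 67% baseline by 8 to 9 points. The simulation does not model the run-in, so its figures are for an observer guessing immediately before each allocation.

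Second, only a journal article is shown. The full protocol may separate enrolling from treating staff, or keep block sizes from sites. That also stands, so silence on those points is not held against the plan. What remains is the stated choice: a size equal to the minimum, and sizes in print.

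Third, this is a pilot whose results the Discussion calls preliminary, and small blocks in small strata are a common choice for balance. This limits the severity. But the balance given up with larger blocks is under one patient per site on average.

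A reader might infer more than the documents support:
- That upcoming assignments are simply predictable, on the logic of a block of 3. The 44% figure holds only if every block were 3, and the article says 3 or 6; the 33% figure needs the block boundaries to be known.
- That the primary contrast is biased. Nothing in the article shows that enrolling staff know the sizes, track the sequence or favour CMT, and no shift in NRS points can be derived from it.
- That all comparisons are exposed. If the placebo matches, the two CMT arms cannot be told apart, so SGHH+CMT versus placebo+CMT is not affected.

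**Conclusion.** The point holds as an avoidable risk of selection bias in contrasts with the SGHH-alone arm, which include the primary one. Its size is about 10% of assignments certain and 75% guessed correctly if only the sizes are known, and 33% certain if block boundaries are known as well. These figures rest on 30 patients per site, equally likely sizes mixed at random, and an observer who sees every earlier CMT/no-CMT assignment at the site. The risk is worth removing because it falls on the primary contrast and the remedy is cheap; bias has not been shown.

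**What to change.** For patients not yet randomised, have the CRO issue new site lists without block size 3, using larger randomly varied blocks (for example 6, 9 and 12). Keep the sizes in a restricted document held by the CRO and withheld from both enrolling and treating staff; choose sizes other than any already published.

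The cost is a new list, a wording change, and a slightly larger possible within-site imbalance (mean range about 0.9 against 0.4 patients at 30 per site). Section 2.5.5 describes t tests and repeated-measures ANOVA with no site term stated, so adjustment cannot be taken for granted: add site to the model for the primary comparison. Arms, sample size and treatment are unchanged.

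If randomisation is already complete, report who enrolled patients, what they knew of the block sizes, and baseline balance by site.

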**Figure 1 F1:**
[figure not shown]
Study flow diagram.

After randomization, the participants will receive medication for 4 weeks, and an additional 4 weeks of follow-up, during which they will visit the clinic once every 2 weeks. To manage adherence to the interventional products, study staff will ask participants to return the unused products for calculating compliance at every visit.

### Interventions

2.3

#### SGHH

2.3.1

SGHH is the granulated traditional herbal extract (manufactured by Hanpoong Pharm and Foods Co., Ltd.) for treating musculoskeletal pains caused by arthritis, sciatica, gout, and back discomfort.^[13]^ Subjects will take 3 g of SGHH per serving with warm water, 3 times a day between meals for 4 weeks. The details of ingredients of SGHH are provided in Table 3.

**Table 3 T3:**
[figure not shown]
Ingredients details of Sogyeonghwalhyeol-tang.

#### Placebo

2.3.2

The placebo will be manufactured to appear similar in appearance to SGHH under strict quality-control systems, such that the participants will not distinguish between the 2. The placebo contains 5.1 g lactose, 3.0 g cornstarch, and 0.3 g *Ssanghwa* herbal flavor.

#### Chuna manual therapy (CMT)

2.3.3

The CMT strategies in this trial are selected after consultation with the scientific committee of the Korean Society of Chuna Manual Medicine for Spine and Nerves (KSCMM).^[14–16]^ Each treatment session conducted by qualified physicians will be 20 to 30 minutes long and will include 3 mandatory and 1 or 2 selective techniques per participant. The CMT physician must be a registered physiatrist of Korean medicine (specialist of physical medicine and rehabilitation) with more than 1 year of clinical experience and should have completed the 126-hour Chuna Manipulative Treatment (CMT) Workshop and have a thorough understanding of study design through an SOP training workshop prior to study initiation. The final selected techniques are presented in detail (Supplemental Digital Content (Appendix 1)).

### Withdrawal and dropout

2.4

Subjects may withdraw from the trial for any reason, without penalty. If a subject indicates his/her wish to withdraw, the site PI may clarify the reason of withdrawal and discontinue participation. Termination from the study will be at the discretion of the PI in the event of protocol violations such as prohibited concomitant medications and inadequate compliance. All the progress notes on trial terminations are documented on the case report forms (CRF) with reasons.

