#### Statistical management

2.5.5

An independent statistician from ISEE who is blinded to the treatment allocation will conduct data analysis by both intent-to-treat (ITT) and per-protocol (PP) analysis. The data analysis strategy for testing each study hypotheses is summarized in Table 4.

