**Table 4 T4:**

Study hypotheses for statistical analysis plan.

Baseline demographic data will be analysed using a *t* test for continuous data and a chi-square test for categorical data. All outcome measures will be calculated as the mean changes between pre- and post-treatments that will be compared using a paired *t* test for intragroup analysis and a Student *t* test for intergroup analysis. Any variables that are to be assessed repeatedly during the trial will be analysed by comparing the mean changes over time using a repeated-measures ANOVA test. Missing data will be using the Last-observation-carried-forward (LOCF) analysis method. There will be no interim analysis for any reason. And we will not establish the data and safety monitoring committee due to the resource and personnel limitations.

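### Section 2.4 lets the PI remove randomised participants from the study for non-adherence; with LOCF this undermines the stated ITT analysis and can bias the primary contrast

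*Protocol article*

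**What the plan says.** Four statements in the protocol article bear on this.

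- **Withdrawal and dropout (2.4).** "Termination from the study will be at the discretion of the PI in the event of protocol violations such as prohibited concomitant medications". The named grounds are "protocol violations such as prohibited concomitant medications and inadequate compliance". What must be kept afterwards is limited to notes and reasons: "All the progress notes on trial terminations are documented on the case report forms (CRF) with reasons". Continued outcome assessment is not mentioned.
- **Statistical management (2.5.5).** The independent statistician "will conduct data analysis by both intent-to-treat (ITT) and per-protocol (PP) analysis". For gaps in the data: "Missing data will be using the Last-observation-carried-forward (LOCF) analysis method".
- **Randomization (2.2.2).** "this trial is designed as an assessor- and analyst-blinded study". Site PIs are not listed among those blinded. The text after Figure 1 says that compliance is calculated from returned product at every visit, and that visits run every two weeks through 4 weeks of treatment and 4 weeks of follow-up.
- **Introduction.** The primary comparison is SGHH with CMT against SGHH alone.

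**The concern.** An ITT analysis estimates the effect in everyone randomised, whatever their adherence. Section 2.4 makes poor adherence a ground for leaving the study. Both named grounds arise after randomisation and may follow from lack of effect or from intolerance, so the participants removed may differ systematically from those who stay. Their real later scores would be replaced by a value taken before termination.

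In the primary contrast one arm receives hands-on treatment and the other does not, so termination rates could differ. The decision is left to the PI's discretion, and the PI is not stated to be blinded to that visible difference. The article also says that this pilot is to supply an effect size for larger trials, so a distorted contrast would carry into their planning.

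**Working it through.** The plan has no figure to reproduce here. The total of 150 is set on feasibility grounds, without alpha, power, effect size or SD. Only the arm size can be derived: 150 / 3 = 50 at 1:1:1.

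**Step 1: read the rules together.** Section 2.4 ends participation in the study. Section 2.5.5 keeps the participant in ITT through LOCF. A terminated participant therefore counts in ITT with a pre-termination score, although scheduled visits remain at which the real score could be taken.

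**Step 2: illustrate the size.** Inputs not in the document, all assumed:
- SD of NRS change 2.0 at weeks 2 and 4, with correlation 0.6 between them
- mean change -1 at week 2 and -2 at week 4 in both arms, so no true difference
- termination at week 2, more likely in poorer responders: a participant is terminated when week-2 change plus independent noise (SD 2.0) exceeds the cut-off giving the assumed share p
- week 4 taken as the post-treatment value, with a t test on change

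Results from 10,000 simulated trials per row. Bias is the first arm minus the second; a positive value makes the first arm look worse.

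| Terminated | LOCF bias | LOCF type I error | Bias if outcomes still collected | Bias if terminated participants are dropped |
|---|---|---|---|---|
| 10% vs 10% | 0.01 | 5.0% | 0.01 | 0.00 |
| 10% vs 5% | 0.09 | 5.0% | 0.00 | -0.07 |
| 15% vs 5% | 0.17 | 6.6% | 0.00 | -0.14 |
| 20% vs 10% | 0.16 | 6.5% | 0.00 | -0.14 |
| 20% vs 5% | 0.25 | 8.6% | 0.00 | -0.20 |
| 30% vs 10% | 0.29 | 10.0% | -0.01 | -0.26 |

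With outcomes still collected, type I error was 4.6% to 5.1% in these rows. The standard error of the contrast is 2.0 x sqrt(2/50) = 0.40, so the simulation error of each bias is about 0.40 / sqrt(10,000) = 0.004.

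**Step 3: check by formula.** Under these assumptions LOCF moves an arm's mean by

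shift(p) = p x m + (1 - 0.6) x 2.0 / sqrt(2) x phi(z),

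where m is the mean further improvement from week 2 to week 4 (here 1), z is the upper-p normal quantile and phi is the normal density.
- p = 5%: 0.05 + 0.566 x 0.103 = 0.108
- p = 10%: 0.10 + 0.566 x 0.175 = 0.199
- p = 30%: 0.30 + 0.566 x 0.348 = 0.497

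The differences are 0.199 - 0.108 = 0.09 and 0.497 - 0.199 = 0.30, in agreement with the simulation.

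**Step 4: direction.** With continuing improvement, LOCF makes the arm with more terminations look worse. If pain instead rose by 1 point on average between the visits (m = -1), the 30% versus 10% difference would be (-0.30 + 0.197) - (-0.10 + 0.099) = -0.10, the opposite sign. Dropping terminated participants also reverses the sign (last column), but that is not the method stated for missing data.

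**The case against.** The strongest reply is that the article condenses a longer protocol that is not shown. Loss of later data is the plain reading of ending participation in the study, but it is not spelled out, and the full protocol may provide for continued assessment. That stands as a limit on certainty. It does not remove the point: the article states a rule, and an analysis plan cannot repair the loss, because outcomes never collected cannot be analysed.

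Several stronger readings are tempting and are not supported.

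- *ITT is defeated, or differs from PP only by carried-forward values.* Termination is discretionary. Violators who stay contribute observed data to ITT and may be left out of PP, which the article does not define. LOCF also formally keeps terminated participants in ITT.
- *The primary contrast is biased, and towards no difference.* No termination rates are given. With equal rates and no true difference the bias is about zero. A shrinking contrast, with more terminations under SGHH alone, is what dropping poor responders would produce; LOCF with continuing improvement would instead enlarge the apparent benefit of CMT.
- *Prohibited medication means pain medication.* The visible text lists no drugs, so the link to pain is plausible but inferred.
- *The PI knows every allocation.* The placebo resembles SGHH, and unblinding goes through the contract research organisation and the sponsor. The blinding concern is confined to the visible manual therapy.

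The trial is also a pilot that admits it may be inconclusive. That lowers the stakes of a single test result, but not of the effect size it is meant to hand on.

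**Conclusion.** The point holds in limited form. As written, Section 2.4 allows outcome data to be lost for post-randomisation reasons plausibly related to treatment, and LOCF then stands in for the real scores. This undermines the ITT analysis and can bias SGHH plus CMT versus SGHH if terminations are related to outcome and unequal between arms.

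Neither size nor sign can be known from the document. Over the assumed unequal rates, the bias is 0.09 to 0.29 NRS points, or 0.09 / 0.40 = 0.22 to 0.29 / 0.40 = 0.73 of a standard error. At the low end type I error does not move. The change is worth making because it is cheap and the loss cannot be repaired afterwards.

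**What to change.** Amend Section 2.4 to separate stopping study treatment from leaving the study. Whatever is decided about treatment, keep collecting NRS, RMDQ, EQ-5D and safety data at all remaining scheduled visits unless the participant withdraws consent to follow-up. Include these data in the ITT analysis. Use compliance and prohibited medication only to define the PP set, and fix that set before the allocation code is opened. If the full protocol already provides for continued assessment, Section 2.4 should say so.

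The cost is a short amendment, with IRB approval, and a few more completed visits that are already in the schedule. No rule on when treatment should stop is proposed.
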